**IV. STUDY DESIGN.**

- a. **Trial Design:** A multi-institution, randomized, single-blind clinical trial
  - b. **Participants and Exclusion Criteria:** Eligible subjects identified from the medical record will be those who are 1) scheduled to undergo RALP surgery, 2) willing to consent to the surgery being performed by one of the surgeons participating in the study, and 3) willing to be assigned by randomization to one of the two groups in the study. Exclusion criteria are 1) prior prostate surgery, ablation, radiation, or androgen deprivation therapy, 2) lack of 3 Tesla or 1.5 Tesla with endorectal coil preoperative MRI imaging, and 3) inability to give informed consent.
  - c. **Randomization:** Each case will be assigned to one of the two preparation methods by a randomization procedure that is stratified by surgeon. Each surgeon-specific randomization schedule will be prepared using permuted blocks of size 2; i.e., each 2-patient block will be some permutation of {VR-aided, Control}. Thus, each surgeon's cases will be randomized in a 1:1 ratio. Use of permuted blocks thus avoids any confounding of preparation method with temporal trends (e.g., trend due to a learning curve.)
- Sequentially numbered opaque sealed envelopes (SNOSEs) will be prepared for each individual surgeon. Each envelope will contain the treatment assignment for one case (intervention or control). There will be an equal number of envelopes containing intervention assignments and control assignments; the total number of envelopes provided to each surgeon will be determined based on the surgeon's historical/anticipated case volume. The treatment code will remain concealed inside the envelope until the moment the case is ready to be prepared.

- d. **Blinding:** Patients, personnel gathering data from the video review, and statistician will be blinded. Control and intervention groups identifiers will be known only to the research personnel opening the sealed envelope for random group assignment and extracting patient data from the electronic medical record.
- e. **Intervention:** For intervention cases, surgeons will be provided with a 3D model to view (a) prior to the operation in addition to the MRI and biopsy results and (b) during the operation in addition to the MRI. For control cases, surgeons will view only the MRI and biopsy results prior to the operation and during the operation itself.

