- h. **Sample Size:** Sample size was calculated using prior data, including previous trials using 3D models in robotic partial nephrectomy. Previously we noted an effect size of 0.44 regarding the difference of outcome measures between 3D

model-aided and control groups. To account for multiple endpoints, we raised the sample size by 15%. Using the above method and paired t-test, the sample size of 90 (45 per arm) provided 80% power to detect clinically significant differences in our primary outcome measures with  $\alpha=0.05$ .

- i. **Statistical analysis:** Initial analysis will compare baseline characteristics between cases performed with (intervention) or without (control) models involved in preoperative planning. A two-sample t-test will be employed to compare means between groups and Chi-Square test or Fisher's exact test to assess the association between categorical variables. For outcome measures, the appropriate test will be used as described above to compare groups. To mitigate type I error due to multiple comparisons, and if the randomization yields balanced cohorts, a Bonferroni correction may be utilized for the primary and secondary outcomes. If randomization yields groups with statistically or clinically significant differences, adjusted differences between groups will be studied using a linear mixed model to regress the endpoint variables on covariates listed above, or the logistic mixed model, as appropriate.

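### On the inputs printed in IV.h, a 15% increase gives 50 per arm rather than 45, so 0.44, 80%, +15% and 90 do not reproduce together unless an unstated input differs

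*Combined protocol and SAP*

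**What the plan says.** The whole calculation is in IV.h (Sample Size).

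- Effect size, from earlier work with 3D models in partial nephrectomy: "Previously we noted an effect size of 0.44 regarding the difference of outcome measures between 3D" model and control cases.
- Allowance: "To account for multiple endpoints, we raised the sample size by 15" per cent.
- Test: "Using the above method and paired t-test".
- Result: "the sample size of 90 (45 per arm) provided 80% power to detect clinically significant differences in our primary outcome measures", at alpha 0.05.

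IV.h does not give the number before the increase, the power at that number, whether alpha is one- or two-sided, the scale of the 0.44 (paired difference or between-group), a within-pair correlation, or a dropout allowance.

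Two other places bear on it. In IV.c, "cases will be randomized in a 1:1 ratio" and "Each surgeon-specific randomization schedule will be prepared using permuted blocks of size 2", which is the only possible source of pairs. In IV.i, the analysis test is not paired: "A two-sample t-test will be employed to compare means between groups".

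**The concern.** The usual way to read IV.h is that a base size was found for 80% power and then raised by 15%. On that reading, 45 per arm should be 15% above the base that the printed inputs require. It is not.

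The 15% is the only allowance for multiplicity in the sizing. IV.g makes the primary outcome a set of measures: margin status, PSA in two forms at 3 to 6 months, PSA above 0.1 at 18 to 24 months, and later androgen deprivation or radiation. IV.i says only that a Bonferroni correction may be used. A reader would therefore rely on a 15% reserve that, on the described method, is about a third of that size.

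**Working it through.** **Inputs.** From IV.h: effect size 0.44, paired t-test, alpha 0.05, power 80%, increase 15%, result 45 per arm. Assumed, because IV.h is silent: two-sided alpha, and 0.44 as the mean paired difference divided by the SD of the differences.

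**Formula.** With n pairs, the test statistic has n − 1 degrees of freedom and noncentrality 0.44 × √n. Power is the probability that a noncentral t exceeds the two-sided 5% critical value in either direction.

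**Attempt to reproduce the plan's figure**

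| Pairs (= per arm) | Power, two-sided |
|---|---|
| 39 | 76.4% |
| 42 | 79.5% |
| 43 | 80.5% |
| 45 | 82.3% |
| 50 | 86.2% |

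1. The smallest n with at least 80% power is 43 per arm (86 in total).
2. Add 15%: 43 × 1.15 = 49.45, so 50 per arm and 100 in total. On the total, 86 × 1.15 = 98.9, so 99. The plan has 45 and 90.
3. Actual margin: 45 / 43 = 1.047, which is 4.7%.
4. Backwards: 45 / 1.15 = 39.1, and 39 × 1.15 = 44.85, so 45. The base would be 39 pairs, with 76.4% power.

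**Variants using the printed 0.44**

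| Variant | Base per arm | After +15% |
|---|---|---|
| 0.44 at the bottom of its rounding range (0.435) | 44 | 50.6, so 51 |
| 0.44 at the top of its rounding range (0.445) | 42 | 48.3, so 49 |
| 15% applied as n / 0.85 | 43 | 50.6, so 51 |
| Normal approximation, (1.960 + 0.842)² / 0.44² = 40.5 | 41 | 46.6 to 47.2, so 47 to 48 |
| One-sided paired t | 34 | 39.1, so 40 |
| Two-sample t, two-sided | 83 | 95.5, so 96 |

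None gives 45 per arm. The nearest two-sided case at 0.44 is the normal approximation, at 94 to 96 in total, and the plan names a t-test.

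**What would reconcile the figures**

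- *A different effect size.* For 39 pairs to have 80% power, the effect size must be about 0.46.
- *A different scale.* If 0.44 is a between-group effect and r is the within-pair correlation, the paired effect is 0.44 / √(2(1 − r)). At r = 0.50 this is 0.44 and the base is 43. At r = 0.55 it is 0.44 / √0.90 = 0.464, the base is 39, and 39 × 1.15 = 44.85, so 45 per arm. At r = 0.60 the base is 35, and 35 × 1.15 = 40.25. The documents give no r.

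**Same inputs under the IV.i test.** A two-sample t-test with 45 per arm has noncentrality 0.44 × √(45/2) = 2.087 on 88 degrees of freedom, giving about 54% power.

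**The case against.** A reader might infer that the printed figures cannot all be true, or that one of the 15% and the 80% must be wrong. The documents do not support either inference, for three reasons.

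- IV.h attaches the power to the final number: "the sample size of 90 (45 per arm) provided 80% power". It never says that the base was sized at 80%. Taken literally, 39 raised by 15% is 45, and 45 pairs give 82.3%, which meets 80%. This stands as a limit on the claim. It leaves a base of 76.4% power, so the increase would have gone mostly to reaching 80% for one endpoint, not to covering several.
- The scale of the 0.44 is unstated. A within-pair correlation of about 0.55 reconciles all four figures. This also stands, so the plan is under-specified rather than proved inconsistent. It does not rescue the text, because that correlation is supplied from outside it.
- Sidedness is unstated. One-sided, 45 is 32% above the base of 34 and more than contains the 15%. It would then be wrong to say that the increase is absent, but a 15% rise would give 40, so the figures still disagree.

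A reader might also infer that about 10 more patients are required. That does not follow: 45 per arm meets 80% for a single endpoint on the plan's own paired method.

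Finally, printing 43 per arm as the requirement without qualification would endorse a paired calculation that IV.i does not carry through. That objection stands and shapes the fix.

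**Conclusion.** The sample size is not reproducible from the inputs IV.h prints. With a paired t-test, 0.44 as the paired-difference effect and two-sided alpha 0.05, the base is 43 per arm and a 15% increase gives 50. The 45 in the plan is 5 per arm short of its stated rule (9 to 10 patients in total) and 4.7% above the base. If the 15% is already inside the 45, the base had 76.4% power.

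The conclusion rests on the two assumptions named, sidedness and effect-size scale. It does not identify which printed item is misreported: the effect size, its scale, the formula, the 15% and the 80% are all candidates. The point concerns a figure that readers rely on. It does not show that 45 per arm misses 80% for one endpoint under the paired test.

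The mismatch between paired sizing and the two-sample analysis in IV.i is a separate and larger matter. It does not explain this discrepancy, since two-sample sizing needs 83 per arm before any increase.

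**What to change.** Keep 90 patients and correct IV.h in one of two ways.

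1. If a calculation behind the 90 exists, print its base number, sidedness, effect-size scale and any within-pair correlation, so that a 15% increase visibly gives 45 per arm.
2. Otherwise, withdraw the statement that a 15% increase for multiple endpoints is included, and say that 45 per arm is about 5% above the 43 that the described paired calculation needs (two-sided, single endpoint).

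In either case, add that the figure applies only to a paired test, and that under the two-sample t-test named in IV.i the same inputs give about 54% power at 45 per arm.

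The cost is a few sentences in IV.h and no extra patients. The downside is that the stated reserve for multiple endpoints becomes less favourable.

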- f. **3D Model Creation and Delivery:** MRI scans will be deidentified and sent in Digital Imaging and Communications in Medicine (DICOM) format to Ceevra, Inc., where a patient-specific 3D model for each intervention patient will be created. The Prostate Imaging-Reporting and Data System (PIRADS) score will be used to identify and label prostate lesions. In addition, the biopsy report, will be used to create a patient-specific pathology map that will be included in the model to assist the surgeon in understanding the location of biopsy-proven cancer within the prostate. Models will be delivered to a mobile application on the surgeon's smartphone (Ceevra Reveal) and viewed as described above. In addition, the surgeon may view the model picture-in-picture on the robotic console screen using a video cable connection between the surgeon's smartphone and the surgical robot.
- g. **Outcomes Measures and Covariates:** The primary outcome measure is oncologic outcomes after RALP. This outcome will be measured at three time points: immediately postoperative, short term, and a final assessment when oncologic and functional outcomes have reached a steady state. Oncologic outcomes will be measured as margin status (positive or negative), PSA (linear and detectable/undetectable) at the initial assessment (which in most cases is three months postoperatively but may occur any time between 3 and 6 months), and PSA ( $>0.1$ ) at the final assessment (to be collected after 18 months but no later than 24 months). Additionally, any use of androgen deprivation therapy or radiation therapy will be captured at 24 months as an adverse oncologic outcome.
- Secondary outcomes are the urinary and sexual function of the patient, measured at the same three time points as above. For urinary function, this is bladder neck sparing (yes or no), measured immediately postoperatively, and incontinence pads per day, measured at both 3-6 months and 18-24 months postoperatively. For sexual function, this is nerve sparing (none, left, right, or bilateral), measured immediately postoperatively, followed by SHIM score, measured at both 3-6 months and 18-24 months postoperatively.
- Demographic data, disease-specific, surgery-specific, and surgeon-specific covariates will be collected from the medical record as well, see Appendix A.

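### The 80% power for 45 per arm rests on a paired t-test, but the trial compares independent arms; unpaired power is about 54% if 0.44 is a two-sided, between-group effect

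*Combined protocol and SAP*

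**What the plan says.** Section IV.h (Sample Size) takes its effect size from earlier trials of 3D models in another robotic operation: "Previously we noted an effect size of 0.44 regarding the difference of outcome measures between 3D" model-aided and control groups. It gives no standard deviation or event rate, and does not say whether 0.44 is a between-group or a paired standardised difference. It adds an allowance for multiplicity, "To account for multiple endpoints, we raised the sample size by 15" per cent, and concludes: "Using the above method and paired t-test, the sample size of 90 (45 per arm) provided 80% power to detect clinically significant differences". Alpha is 0.05, with no statement of one or two sides.

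The design is parallel-group. Section IV.c (Randomization) gives each case one preparation method, using blocks of 2 within surgeon, so that "each surgeon's cases will be randomized in a 1:1 ratio". It justifies the blocks as protection against time trends such as a learning curve.

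Section IV.i (Statistical analysis) is unpaired: "A two-sample t-test will be employed to compare means between groups", with chi-square or Fisher's exact test for categorical variables. The same tests are carried over to the outcomes. Mixed models come in if the groups turn out unbalanced.

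Section IV.g describes the primary outcome: "Oncologic outcomes will be measured as margin status (positive or negative), PSA (linear and detectable/undetectable) at the initial assessment". It then adds PSA above 0.1 at the final assessment and any use of androgen deprivation or radiation therapy.

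**The concern.** No patient is his own control, and no analysis pairs one patient with another, so a paired t-test does not describe the comparison to be made. The choice matters. At the same numerical effect size, and without strong correlation between arms, an unpaired comparison needs roughly twice as many patients per arm as a paired test needs pairs. The figure of 45 looks like a number of pairs used as a number of patients per arm.

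The 80% is the protocol's only justification for 90 patients, and it is claimed for the primary outcomes. If it is too high, a null result would be read as coming from a well-powered trial when the chance of detecting the planned effect may be close to one in two.

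**Working it through.** **Inputs.** Effect size 0.44, alpha 0.05, 45 per arm, 80% power and the 15% increase are all from IV.h. Independent arms at 1:1 are from IV.c, and the unpaired tests from IV.i. *Assumptions:* two-sided alpha unless stated otherwise; 0.44 is a between-group difference in steps 2 and 3, and a paired effect in step 4. Power is from the noncentral t distribution.

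**1. The plan's own figure (paired).** Noncentrality = d × √n, with n − 1 degrees of freedom.
- 45 pairs: 0.44 × √45 = 2.95, power 82.3%.
- For 80% power: n = 42.5, so 43 pairs.
- Normal approximation: (1.96 + 0.84)² / 0.44² ≈ 40.5; with the increase, 40.5 × 1.15 ≈ 46.6.
- Exact t with the increase: 42.5 × 1.15 = 48.9, or 43 × 1.15 = 49.45.

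So 45 is close to what a paired test gives, although how the 15% entered cannot be recovered.

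**2. The planned comparison (unpaired).** Noncentrality = d × √(n/2), with 2n − 2 degrees of freedom.
- 45 per arm: 0.44 × √22.5 = 2.09, power **54.2%**.
- One-sided alpha of 0.05: 66.5%.
- For 80% power at 0.44: n = 82.05, so 83 per arm (166 in total).
- Difference detectable with 80% power at 45 per arm: 0.597, about 0.60.

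**3. Blocks of 2 analysed as pairs, between-group d = 0.44.** The paired effect is 0.44 / √(2(1 − ρ)), where ρ is the within-pair correlation.

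| ρ | paired effect | power, 45 pairs |
|---|---|---|
| 0 | 0.31 | 53% |
| 0.1 | 0.33 | 58% |
| 0.3 | 0.37 | 68% |
| 0.5 | 0.44 | 82% |

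**4. If 0.44 was itself a paired effect.** The between-group difference is then 0.44 × √(2(1 − ρ)), tested unpaired with 45 per arm.

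| ρ | between-group d | power |
|---|---|---|
| 0 | 0.62 | 83% |
| 0.1 | 0.59 | 79% |
| 0.3 | 0.52 | 69% |
| 0.5 | 0.44 | 54% |

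**5. Multiplicity, as a scenario.** IV.g can be counted as five primary measures (margin status; early PSA as a continuous value; early PSA detectable or not; late PSA above 0.1; androgen deprivation or radiation). It has six secondary ones (bladder neck sparing; pads at two times; nerve sparing; SHIM at two times). With d = 0.44 and 45 per arm:
- Bonferroni over 5: alpha = 0.05/5 = 0.01, power about 30%.
- Bonferroni over 11: alpha = 0.05/11 = 0.0045, power about 21%.

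**6. Binary measures.** Four of the five primary measures are binary. If 0.44 is read as Cohen's h, with control rates of 10% to 40% (assumed; the protocol gives none), exact enumeration at 45 per arm gives 51% to 57% power by uncorrected chi-square and 21% to 46% by Fisher's exact test.

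**The case against.** The strongest defence is that 0.44 may be a paired effect, since that is the input a paired t-test calculation takes. Step 4 shows that at low correlations the stated 80% would then roughly hold for the unpaired comparison. This stands in part. The wording of IV.h, a difference between the model-aided and control groups, favours the between-group reading but does not settle it. A reader might infer that the trial simply has 54% power; the documents support that only under the stated reading of 0.44 and a two-sided alpha. The defence still leaves IV.h short, because it gives no correlation from which 80% could be derived.

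A one-sided alpha would help, but 66.5% is still below 80%.

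The blocks of 2 could be called pairs. IV.c does not present them as matching and IV.i does not analyse them that way. Even if it did, a correlation of about 0.5 would be needed. It is tempting to add that a shared surgeon could not produce such a correlation, but the documents give no figure on this, so only the range can be shown.

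A reader might also infer that 45 is an arithmetic error, because the exact paired calculation with the increase gives 49 to 50. That goes too far: 45 is near both the 43 pairs without the increase and the 46.6 from the normal approximation with it. What is unclear is how the 15% was applied.

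Finally, 30% or 21% should not be taken as the plan's own power. IV.i makes the Bonferroni correction optional and conditional on balanced groups, and the counts of 5 and 11 are a tally of IV.g.

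**Conclusion.** The stated power is wrong as written: it is attached to a paired t-test, while the design and analysis sections specify independent arms and unpaired tests. On the reading that the wording of IV.h favours, with a two-sided alpha, power at 45 per arm is about 54% rather than 80%, and the difference detectable with 80% power is about 0.60 rather than 0.44. If 0.44 was a paired effect, power lies between 83% and 54% for correlations from 0 to 0.5, and only the sponsor can say which applies. In neither case does a t-test figure describe the binary primary measures. The mismatch itself is certain; the size of the shortfall is conditional on what 0.44 measures and on the sidedness. This should be corrected, because 80% is the sole support for the sample size.

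**What to change.** Keep 90 patients and revise IV.h:

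- Delete the reference to a paired t-test. State whether 0.44 is a between-group or a paired standardised difference, and whether alpha is one- or two-sided.
- If it is between-group and two-sided, state: *With 45 per arm, a two-sided two-sample t-test at alpha = 0.05 has about 54% power for a between-group standardised difference of 0.44 and 80% power for 0.60.* If it was a paired effect, give the correlation, the implied between-group difference and the unpaired power.
- Remove the claim that a 15% increase accounts for multiple endpoints. If the optional Bonferroni correction is kept, give power at the corrected alpha as a scenario (about 30% for 5 tests, 21% for 11).
- For the binary outcomes, give power for a named test, using the sponsor's own control rate. The test must be named: an assumed 25% versus 5%, for example, has 81% power by chi-square but 71% by Fisher's exact test, and IV.i permits either. That pair of rates is not in the documents and should not be written into the protocol.

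The cost is protocol wording and, on the favoured reading, a less favourable stated power. No extra patients and no change of design are needed.

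### The 80% power claim allows nothing for loss to follow-up, although outcomes run to 18-24 months and the per-visit tests use only men with a late value; power is already below 80% with complete data

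*Combined protocol and SAP*

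**What the plan says.** Section IV.h starts from a standardised effect: "Previously we noted an effect size of 0.44 regarding the difference of outcome measures between 3D" model-aided and control cases. It then states "To account for multiple endpoints, we raised the sample size by 15" per cent. The calculation is introduced with "Using the above method and paired t-test" and ends with the claim that "the sample size of 90 (45 per arm) provided 80% power to detect clinically significant differences in our primary outcome measures", at alpha 0.05. Sidedness is not stated.

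Section IV.g places part of the primary outcome late. PSA above 0.1 is assessed at the final visit ("to be collected after 18 months but no later than 24 months"), and any androgen deprivation or radiation therapy is captured at 24 months. The secondary measures SHIM and pads per day are recorded twice after surgery, at 3-6 and at 18-24 months.

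On allocation, section IV.c says that each surgeon's "cases will be randomized in a 1:1 ratio". Section IV.i names the tests: "A two-sample t-test will be employed to compare means between groups and Chi-Square test or Fisher's exact test" for categorical variables. It then adds "For outcome measures, the appropriate test will be used as described above to compare groups". A linear or logistic mixed model enters only if the groups turn out to differ, and it regresses an endpoint on covariates. The text available for review gives no loss rate, no allowance for loss and no method for missing values. Section III is not in that text.

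**The concern.** A power figure for an 18-24 month outcome depends on how many men have a value at that time. The plan calculates as if all 90 will. A t-test, chi-square test or Fisher test at one visit leaves out a man with no value at that visit, even when his SHIM score and pad count at 3-6 months are on file.

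Two things are at stake. First, the late comparisons, which the plan treats as the steady-state assessment, would have less power than a reader of IV.h would expect. Second, if men with poor early recovery are less likely to have a late value, a comparison of completers can be biased, and the information that could reduce that bias has been collected but is not used.

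**Working it through.** **Inputs.** From the plan: effect size d = 0.44, 45 per arm, alpha 0.05, paired t-test for sizing, 15% inflation for multiple endpoints (IV.h); 1:1 allocation to two separate groups (IV.c); two-sample t-test for means (IV.i). Assumed: two-sided testing, loss of 10% or 20%, and correlation of 0.5-0.7 between the two postoperative SHIM scores. Power is from the exact noncentral t distribution.

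**1. The plan's own figure.** For a paired t-test the noncentrality is d × √n, with n pairs.
- 80% power needs n = 42.5, so 43 pairs. With the 15%: 43 × 1.15 = 49.45, so 50, not 45.
- The normal approximation gives 41 pairs, and 41 × 1.15 = 47.15, so 48.
- One-sided, 34 pairs are needed, and 34 × 1.15 = 39.1, so 40.
- Backwards: 45 / 1.15 = 39.1, and 39 pairs have 76.4% power (two-sided t).

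None of these gives 45. If the 15% is left out, 45 pairs have 82.3% power, which is the reading most favourable to the plan.

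**2. Loss on that favourable reading.**

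| Complete pairs | Power |
|---|---|
| 45 | 82.3% |
| 44 | 81.4% |
| 43 | 80.5% |
| 42 | 79.5% |
| 41 | 78.5% |

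The 80% survives two lost pairs and fails at the third. A pair is lost when either man is missing, so two missing men in each arm can cost four pairs (41 left, 78.5%). If loss is independent between the members of a pair, 10% leaves 45 × 0.9² = 36.5 pairs (73%) and 20% leaves 45 × 0.8² = 28.8 pairs (about 63%).

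**3. The test that IV.i names.** For two independent arms of n the noncentrality is d × √(n/2).

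| Loss | n per arm | Noncentrality | Power |
|---|---|---|---|
| none | 45 | 0.44 × √22.5 = 2.09 | 54.2% |
| 10% | 40.5 | 0.44 × √20.25 = 1.98 | 49.8% |
| 20% | 36 | 0.44 × √18 = 1.87 | 45.3% |

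With complete data, the effect detectable with 80% power at 45 per arm is 0.60. Most of the shortfall against 80% is therefore present before anyone is lost: about 26 points (80 − 54.2), with a further 4 to 9 points from loss.

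**4. What the 3-6 month value would add for SHIM.** Let m be the share without a late value and ρ the correlation between visits. Relative to complete data, the variance of the late contrast is approximately
- completers only: 1/(1 − m)
- repeated-measures model: 1 + [m/(1 − m)] × (1 − ρ²)

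At m = 0.2 these are 1.25 against 1.1875 (ρ = 0.5) or 1.1275 (ρ = 0.7), a reduction of 5% to 10%. The effective size rises from 36 to 36/0.95 = 37.9 or 36/0.902 = 39.9 per arm, and two-sample power from about 45% to about 47-49%. At m = 0.3 the reduction is about 7.5% to 15%.

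**5. Bias.** In a simulation, the log-odds of having a late value rose by 1 per SD of early SHIM (odds ratio 2.7) in both arms, the true difference was 0.44 SD at both visits, and loss was 20%. The completers' difference was too small by about 0.03 SD. If the arms do not differ at 3-6 months, this mechanism produces no bias in the difference.

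**The case against.** The strongest reply is that the documents give no basis for any loss rate. Case data come from the site's electronic record (VIII.a), so a late PSA or a treatment record may be available without a study visit, and the final assessment has a window of several months. Nor does IV.i say that men without a late value are excluded. This stands in part: the 10% and 20% are assumptions, and loss may be small. Exclusion is an inference, but it follows from how the named tests work, and the conditional mixed model is not described as bringing in the earlier visit.

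A second reply is that the larger defect is sizing on a paired test for independent arms, with loss a minor addition. That is correct, and the size of this point is set accordingly. Correcting the test would still leave no allowance for loss and no method for missing values.

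A reader might go further and infer that the 80% holds until a third man per arm is missing. The documents do not support that threshold. The limit of two applies to pairs, only on a two-sided paired test, and only if the 15% is treated as spare although IV.h assigns it to multiple endpoints. The comparison named in IV.i is two-sample, where power is about 54% with nobody missing. Nor can a t-test threshold be carried over to the late primary measures, PSA above 0.1 and androgen deprivation or radiation: both are binary, and no rates are given.

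**Conclusion.** The point holds, as a minor one. The stated 80% includes no allowance for loss, and the named per-visit tests leave out men without a late value. For a continuous measure at d = 0.44 and two-sided 0.05, power is about 54% with complete data and about 50% or 45% at an assumed 10% or 20% loss. On the plan's paired calculation without the 15%, 80% is lost at the third lost pair. For the late primary measures the direction is clear, since fewer men means less power, but no figure can be given.

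Using both postoperative visits helps only modestly, and only for SHIM and pads per day, which are secondary. The variance gain rests on the assumed loss and correlation. The bias of about 0.03 SD arises only if return depends on early SHIM and the arms already differ at 3-6 months.

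**What to change.** 1. **Section IV.h.** Keep 90 men. State that the power figure assumes complete follow-up. Restate it for the two-sample t-test at 45 per arm with complete data and at assumed losses of 10% and 20% (about 54%, 50% and 45% at d = 0.44, two-sided 0.05). Limit this statement to continuous measures.
2. **Section IV.i.** Analyse SHIM with one repeated-measures linear mixed model containing both postoperative visits, arm, visit and arm-by-visit, and report the 18-24 month contrast. Use a repeated ordinal or count model in the same way for pads per day. Men with only a 3-6 month value then stay in the analysis.

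The cost is a few sentences of protocol text, slightly more analysis work and a less favourable stated power. No extra patients or visits are needed. The models do nothing for missing late PSA or treatment data.

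### The multiplicity correction is optional and tied to baseline balance, so the stated alpha of 0.05 is not guaranteed for a claim on the multi-part primary outcome

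*Combined protocol and SAP*

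**What the plan says.** Section IV.g introduces a single primary outcome: "The primary outcome measure is oncologic outcomes after RALP". It then lists several measures: "Oncologic outcomes will be measured as margin status (positive or negative), PSA (linear and detectable/undetectable) at the initial assessment", followed by a PSA threshold of 0.1 at 18 to 24 months. It adds that "any use of androgen deprivation therapy or radiation therapy will be captured at 24 months as an adverse oncologic outcome". No measure or time point is named as decisive, and there is no composite, hierarchy or success rule.

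The secondary outcomes in the same section give six more comparisons: bladder neck sparing, nerve sparing, "incontinence pads per day, measured at both 3-6 months and 18-24 months postoperatively", and SHIM score at the same two later time points.

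Section IV.i contains the only provision on type I error: "if the randomization yields balanced cohorts, a Bonferroni correction may be utilized for the primary and secondary outcomes". The next sentence covers the other case: "If randomization yields groups with statistically or clinically significant differences, adjusted differences between groups will be studied using a linear mixed model" (or a logistic mixed model). It mentions no correction. The number of tests in the family and the per-test level are not given.

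Section IV.h sets alpha at 0.05 and raises the sample size by 15% on account of multiple endpoints.

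**The concern.** A multiplicity rule should depend on how many hypotheses can support the claim. Here it depends on whether the arms resemble each other at baseline, which is a different matter. Covariate adjustment deals with imbalance and does nothing about the number of tests. In the imbalanced case the plan moves to adjusted models and is silent on correction. In the balanced case the word *may* still leaves the choice open.

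Because no oncologic measure is decisive, a nominal p below 0.05 on any one of them could be reported as improved oncologic outcomes. That is the trial's main claim, and the plan does not ensure that it carries a 5% error rate.

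**Working it through.** **Inputs.** From IV.h: alpha 0.05 (sidedness not stated; two-sided assumed), effect size 0.44, paired t-test, 80% power, +15%, 45 per arm. From IV.i: two-sample t-test, chi-square or Fisher's exact test. From IV.g, the primary tests: margin status; linear PSA and detectable PSA at 3–6 months; PSA above 0.1 at 18–24 months; androgen deprivation or radiation use. That is five. It is four if therapy use is only recorded and not tested, and six if the two therapies are tested separately. The secondary tests number six.

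**1. The plan's own figure.** The plan states no family-wise error rate; its only related figure is the sample size.
- Paired, normal approximation: (1.960 + 0.842)² / 0.44² = 40.5, so 41 pairs. The exact t calculation gives 43.
- Adding 15%: 43 × 1.15 = 49.5, so 50 pairs.
- The stated 45 per arm is not reproduced once the 15% is included. The nearest match is 43 pairs without it.
- Power with 45 is 82.3% for the paired t-test and 54.2% for the two-sample t-test that IV.i specifies.

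**2. What the 15% buys.** At 80% power, 15% more patients allows a smaller per-test alpha. The critical value becomes 2.802 × √1.15 − 0.842 = 2.163, a two-sided alpha of about 0.031. Bonferroni would need about +21% for two tests and +49% for five. In any case, IV.h keeps alpha at 0.05. More patients raise power; they do not lower type I error.

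**3. Family-wise error with every test at 0.05 (1 − 0.95^k, independent tests).**

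| Tests | Error |
|---|---|
| 4 | 18.5% |
| 5 | 22.6% |
| 6 | 26.5% |
| 11 (primary and secondary) | 43.1% |

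**4. Allowing for correlation.** The two early PSA measures come from one value, so independence is too pessimistic. Five equally correlated normal test statistics (400,000 simulated draws) give:

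| Correlation | Error |
|---|---|
| 0.3 | 21% |
| 0.5 | 18% |
| 0.7 | 15% |
| 0.9 | 10% |

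**5. Allowing for Fisher's conservatism.** Event rates are not in the documents; 5–30% is assumed. At 45 per arm, the exact size of Fisher's test is 0.0057 at a 5% event rate and 0.0296 at 30%. One t-test at 0.05 plus four independent Fisher tests gives:
- 5% rate: 1 − 0.95 × (1 − 0.0057)⁴ = 7.1%
- 30% rate: 1 − 0.95 × (1 − 0.0296)⁴ = 15.8%

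The uncorrected chi-square test in place of Fisher's gives 22–26%.

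**6. With a mandatory correction.** Five tests at 0.05/5 = 0.01: 1 − 0.99⁵ = 4.9% if independent, and less with positive correlation.

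**7. Cost in power.** At effect size 0.44 and 45 per arm, two-sample t-test power is 54% at 0.05 and 30% at 0.01. For 80% power at 0.01, 123 per arm would be needed. The effect size is a standardised mean difference, so these figures apply directly only to linear PSA.

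**8. Which gate to the secondary outcomes is safe.** Suppose one primary effect is overwhelming and every other null hypothesis is true. If any one primary success opens the six secondary tests at full alpha:
- Holm on the four remaining primary tests: 1 − (1 − 0.0125)⁴ = 4.91%
- Holm on the six secondary tests: 1 − (1 − 0.05/6)⁶ = 4.90%
- Jointly, if independent: 1 − 0.9509 × 0.9510 = 9.6%. Simulation gives 8.6% at correlation 0.3 and 7.3% at 0.5.

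If all primary tests must succeed first, a false secondary claim with any true primary null requires that null to have been rejected already. That event is counted within the 5%, so joint error stays at or below about 5%.

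**The case against.** The strongest reply is that the plan recognises multiplicity: it names Bonferroni and enlarges the sample for multiple endpoints. If Bonferroni is applied over the whole family, the error rate is at or below 5%. This stands as far as it goes. A reader might infer that the trial's false-positive rate *is* 23%, but the documents do not support that. They leave the rate open, and 23% is the figure for five independent, uncorrected tests.

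A reader might also infer exactly five primary tests. IV.g supports four to six, because therapy use is described as captured and two therapies are named. The conclusion is the same for each count.

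A third tempting reading is that the correction will be chosen after outcomes are seen. The stated trigger is the baseline comparison, and IV.d blinds the statistician. Section IX.c schedules monthly reports of results to date without saying whether they are by arm. What the text shows is that *may* does not rule out a later choice, not that one is planned.

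Finally, choosing Bonferroni over the more powerful Holm procedure is a matter of preference. A mandatory Bonferroni correction would cure the defect. The sample-size reply fails, because extra patients do not control type I error.

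**Conclusion.** The rule in IV.i is wrong as written. It makes the only type I error control discretionary, attaches it to a condition unrelated to the number of tests, and states none for the adjusted analysis. With no deciding test in IV.g, alpha of 0.05 is not guaranteed for the claim that oncologic outcomes improved.

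Every uncorrected scenario computed exceeds 5%. A fair range under the stated assumptions is about 7–23%, with the independence figure near the top. The range rests on two-sided tests, a count of five, equal correlations in one set of scenarios, and assumed event rates with independent tests in the other. Correlation and Fisher's conservatism were not combined; together they would lower the figure further. The fault governs the main claim and can be cured by wording, so it should be corrected before outcomes are analysed.

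**What to change.** In IV.i, delete the balance condition and the word *may*. State, before outcomes are analysed, one of two rules:

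- **One family.** List the primary oncologic tests by name. They are always tested at a two-sided family-wise 0.05 by Holm or Bonferroni, whether the analysis is unadjusted or adjusted.
- **One endpoint.** Name a single primary oncologic endpoint and time point, tested at 0.05, and make the other oncologic measures secondary.

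Under either rule, report secondary outcomes with confidence intervals and no confirmatory claim, or test them by Holm only if all primary tests succeed. Opening them after any one primary success should not be adopted if joint control is intended.

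The change itself is wording, but the first option has a real cost that the plan should state. With five tests the first step is at 0.01, and at the plan's effect size and 45 per arm two-sample power falls from about 54% to about 30%. Some nominally significant results would also no longer support a claim. The second option avoids the loss of power, but only the named endpoint then carries the primary claim.
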